### 182 I.2. Postoperative radiotherapy for early stage cancers of 183 the oral cavity and oropharynx

#### 184 I.2.1 Postoperative brachytherapy

185 Brachytherapy is a highly conformal technique that allows a high dose to be delivered, in a  
186 small volume, in a short time (13–15). However, it is not always feasible: involvement of the gum or  
187 retromolar trigon, a distance of less than 5 mm from the gum, infiltration of the intermaxillary  
188 commissure, or extension to the parapharynx, to the cavum for an oropharyngeal tumor, to the union  
189 of the three folds or to the larynx. In addition, brachytherapy requires highly trained teams,  
190 hospitalization of the patient, general anesthesia, and adapted infrastructure.

191 Goineau et al. (16) reported the results of 112 patients treated with postoperative low-dose-  
192 rate (LDR) interstitial brachytherapy by Ir for squamous cell carcinomas of the mobile tongue. The  
193 local control rate at 2 years was 79% and at 5 years was 76%. The overall survival rate at 2 years was  
194 72% and at 5 years was 56%. 22% of patients experienced radionecrosis requiring surgery. 8% of  
195 patients presented with chronic pain requiring the use of morphine. These results were similar to those  
196 of other smaller retrospective studies (13,17,18). In the study by Lapeyre et al. (18) the local control  
197 rate was 81% and the 5-year overall survival rate was 70% for patients with T1/T2-N0 tumors. Strnad

et al. (19) reported the results of the largest brachytherapy study with 385 patients. Patients were treated with pulsed flow brachytherapy (PDR). Brachytherapy was postoperative in 85% of cases. The local control and overall 5-year survival rates were 85% and 69% respectively. The rates of severe late toxicity of mucosal ulceration and osteoradionecrosis were 10 and 5%, respectively.

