### IV. RESEARCH DESIGN

#### IV.1. Primary endpoint

**Rate of patients with late toxicity at 2 years grade  $\geq 3$**  according to the NCI - CTCAE V4.03 classification in connection with hypofractionated stereotactic radiotherapy, i.e. grade  $\geq 3$  toxicities occurring beyond 3 months after the end of stereotactic radiotherapy.

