### 535 ***VI.5.1 Assessment during immediate follow-up visits***

#### 536 **Follow-up visit at 14±3 days after the last stereotactic radiation therapy session**

- 537 • Clinical examination including weight  
 538 • Assessment of general condition according to WHO status  
 539 • Tumor bed examination (clinical +/- nasofibroscopy)  
 540 • Examination of the mouth, throat and neck

- 541 • Type of feed (Solid, liquid, mixed...)
- 542 • Acute toxicity assessments according to NCI-CTCAE v.4.03
- 543 • Collection of concomitant treatments

544

545 **Follow-up visit at 30±5 days after the last stereotactic radiotherapy session**

- 546 • Clinical examination including weight
- 547 • Assessment of general condition according to WHO status
- 548 • Tumor bed examination (clinical +/- nasofibroscopy)
- 549 • Examination of the mouth, throat and neck
- 550 • Type of feed (solid, liquid, mixed, etc.)
- 551 • Acute toxicity assessments according to NCI-CTCAE v.4.03
- 552 • Collection of concomitant treatments
- 553 • EORTC QLQ-C30 and H&N35 Questionnaire

554

555 **Follow-up at 3 months ±10 days after the last stereotactic radiation therapy session**

- 556 • Clinical examination including weight
- 557 • Assessment of general condition according to WHO status
- 558 • Tumor bed examination (clinical +/- nasofibroscopy)
- 559 • Examination of the mouth, throat and neck
- 560 • Type of feed (solid, liquid, mixed, etc.)
- 561 • Acute toxicity assessments according to NCI-CTCAE v.4.03
- 562 • Carcinologic evaluation:
  - 563 ❖ CT scan or cervicofacial MRI (*The choice between MRI and CT is left to the*
  - 564 *discretion of the investigator but follow-ups must be carried out with the same*
  - 565 *technique)*
  - 566 ❖ Chest CT scan (*The use of PET-FDG is left to the choice of the investigators in each*
  - 567 *center if it is medically indicated)*

568

569

570 **VI.5.2 Assessment during long-term monitoring visits**

571 These visits will take place every **3 months±10 days for up to 2 years** after stereotactic radiotherapy

572 and include:

- 573 • Clinical examination including weight
- 574 • Assessment of general condition according to WHO status
- 575 • Tumor bed examination (clinical +/- nasofibroscopy)

- 576 • Examination of the mouth, throat and neck
- 577 • Type of feed (solid, liquid, mixed, etc.)
- 578 • Late toxicity assessments according to NCI-CTCAE v.4.03
- 579 • Carcinologic assessment at **12 months and 24 months**

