### 588 ***VI.5.3 Follow-up on recidivism***

- 589 In the event of local, regional, locoregional or distant recurrence, patients will be monitored only for
- 590 their vital status.
- 591 Data from salvage treatments will be collected in the CRF.
- 592

Table 1: Flow chart

| PERIODE DE L'ESSAI                                                                                                                                                                                                                                                                                                                                                                                                                   | BILAN A L'INCLUSION                  | SUIVI PENDANT LA RADIOTHERAPIE |       | VISITES DE SUIVI POST RADIOTHERAPIE STEREOTAXIQUE |            |                  |                                |                 |                   |                   |                   |                   |                   |
|--------------------------------------------------------------------------------------------------------------------------------------------------------------------------------------------------------------------------------------------------------------------------------------------------------------------------------------------------------------------------------------------------------------------------------------|--------------------------------------|--------------------------------|-------|---------------------------------------------------|------------|------------------|--------------------------------|-----------------|-------------------|-------------------|-------------------|-------------------|-------------------|
| Visites n°                                                                                                                                                                                                                                                                                                                                                                                                                           | V0                                   | V1                             | V2    | V3                                                | V4         | V5               | V6                             | V7              | V8                | V9                | V10               | V11               | V12               |

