| Test de grossesse doit être réalisé dans les 14 jours maximum avant le début de la radiothérapie stéréotaxique
Scanner thoracique: A refaire à l'inclusion uniquement si le délai entre le scanner thoracique préopératoire et la date de début de la radiothérapie est supérieur à 3 mois.
En cas de récurrence locale, régionale, locorégionale et/ou à distance, les patients seront suivis uniquement pour le statut vital |                                      |                                |       |                                                   |            |                  |                                |                 |                   |                   |                   |                   |                   |

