### IX.1. Number of topics to include

881 To determine the number of patients needed, two objectives were considered: severe late toxicity at  
882 2 years (primary outcome) and local control rate at 2 years (secondary outcome). The experimental  
883 design follows a one-step Fleming design with no intermediate analysis due to the primary endpoint  
884 which will be evaluated at 2 years (severe late toxicity).

885 The safety and efficacy profile of hypofractionated stereotactic radiotherapy of the operative bed is  
886 expected to be equivalent to other radiotherapy techniques (brachytherapy or normofractionated  
887 IMRT) (cf 3. Rationale of the study for details). In brachytherapy, the rate of late soft tissue ulceration  
888 is around 10-20% and the rate of bone necrosis is around 5-10%. We have decided: 1/ to accept a rate  
889 of less than 5% and 2/ to reject a rate of more than 15%. With a unilateral test for significance ( $\alpha=0.05$ )  
890 with a power of 90% ( $\beta=0.10$ ), the minimum number of patients to be included is 67.  
891 Hypofractionated stereotactic radiotherapy of the operative bed will then be considered an  
892 unacceptable treatment if 6/67 patients (9%) or more have severe late toxicity (grade  $\geq 3$ ).

893 The local control rate of hypofractionated stereotactic radiotherapy is expected to be equivalent to  
894 other radiotherapy techniques (brachytherapy or normofractionated IMRT). We have decided: (i) to  
895 accept a rate of more than 90% and (ii) to reject a rate of less than 80%. With a one-sided significance  
896 test ( $\alpha=0.05$ ) with a power of 80% ( $\beta=0.20$ ), the minimum number of patients to be included is 83.  
897 A lower potency was decided for control as a secondary outcome. Hypofractionated stereotactic  
898 radiotherapy of the operative bed will then be considered an acceptable treatment if 72/83 patients  
899 (87%) or more are locally controlled at 2 years.

900 As a result of these results, and to compensate for possible loss to follow-up, a total of 90 patients  
901 will be included in this study.

902 As the primary objective of this study is estimated at 2 years, once 30 patients have been included  
903 (33% of inclusions), a review of all grade  $\geq 3$  toxicities will be communicated to the independent trial  
904 monitoring committee (IDSMC = *Independent Data and Safety Monitoring Committee*). The grade 4  

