### 933 **IX.3. Main analysis**

934 The analysis of the main objective, i.e. the rate of severe toxicity of grade  $\geq 3$  to 2 years, with its 95%  
 935 CI will be compared to 15% (with regard to the assumptions set in the context of the estimation of  
 936 the number of subjects needed). If the 95% CI does not include this rate, the trial will be considered  
 937 positive. For efficacy endpoints, 95% bilateral confidence intervals will be provided. Statistical  
 938 analysis will be performed on an intention-to-treat basis.

939 An analysis of the predictive factors of severe toxicity of grade  $\geq 3$  to 2 years will be performed. A  
 940 univariate analysis will be performed using the usual tests: Student's test or Mann-Whitney test if the  
 941 conditions of the t-test are not met (normality, and homoscedasticity studied by the Fisher-Snedecor  
 942 test) for quantitative variables and Chi2 test or Fisher's exact test for categorical variables. The  
 943 multivariate analysis will consider a logistic regression model for binary dependent variable.  
 944 Covariates will be retained based on the results of univariate analysis and their clinical relevance.

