## 1091 **XI.2. Reporting of serious adverse events**

### 1092 ***XI.2.1 Responsibility of the Investigator***

1093 For each type of research involving humans, the investigator records the adverse events or adverse  
1094 analytical findings defined in the protocol as decisive for the safety assessment, keeps a paper trail  
1095 and notifies them to the sponsor.

1096 The investigator is responsible for reporting all adverse events in the case report form.

1097 The severity or grade of the event should be assessed according to the toxicity criteria NCI-CTCAE-  
1098 v.4.03 (*Appendix 1*).

1099 The investigator shall inform the sponsor of all serious adverse events that have occurred in  
 1100 participants, unless otherwise provided for in the protocol.

1101 The investigator is responsible for the appropriate medical follow-up of patients until the resolution  
 1102 or stabilization of the event or until the patient's death. This may sometimes mean that this follow-up  
 1103 continues after the patient has been discharged from the trial.

1104 It transmits the additional information to the study's pharmacovigilance using a SAE reporting form.  
 1105 It also transmits the latest follow-up to the resolution or stabilisation of the SAE.

1106 It keeps the documents concerning the presumed adverse event in order to allow, if necessary, to  
 1107 complete the information previously transmitted.

1108 It responds to requests for additional information from pharmacovigilance in order to document the  
 1109 initial observation and implements the SPONSOR's decisions in relation to SAEs.

1110 The investigator shall notify the sponsor without delay from the day on which it becomes aware of  
 1111 any serious adverse event that has occurred in any patient included

- 1112 - - for the entire duration of the study (up to 2 years after the end of stereotactic radiotherapy),
- 1113 - After the trial has been stopped, regardless of the time limit, provided that no cause other than  
 1114 research can reasonably be incriminated,

1115 on a "Serious Adverse Event" form indicating the date of occurrence, intensity, relationship with the  
 1116 treatment (or research) evaluated, and follow-up.

1117 The narrative report must be completed and sent to the promoter as soon as new relevant information  
 1118 is obtained. Depending on the nature and severity of the event, copies of the patient's anonymized  

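### Scheduled grading of late toxicity stops at recurrence, and the protocol does not say how patients who recur enter the primary toxicity rate

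*Protocol*

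**What the plan says.** Section IV.1 defines the primary endpoint as "Rate of patients with late toxicity at 2 years grade" ≥3 on CTCAE v4.03, related to the stereotactic treatment and occurring more than 3 months after it ends. The grading takes place at the three-monthly long-term visits in VI.5.2, which list "Late toxicity assessments according to NCI-CTCAE v.4.03".

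Section VI.5.3 then limits follow-up: "In the event of local, regional, locoregional or distant recurrence, patients will be monitored only for" vital status, with salvage treatment data also collected. The Table 1 footnote repeats the rule: "les patients seront suivis uniquement pour le statut vital".

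The safety sections read differently. XI.2.1 makes the investigator responsible for entering all adverse events in the case report form. It requires serious events in any included patient "for the entire duration of the study (up to 2 years after the end of stereotactic radiotherapy"). XI.2.2 asks for serious and non-serious events, with start date, grade and causality. Neither section ends at recurrence.

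For the analysis, IX.3 compares the rate and its 95% confidence interval with 15% and says that "analysis will be performed on an intention-to-treat basis". IX.1 gives the design rule as a count: "unacceptable treatment if 6/67 patients (9%) or more have severe late toxicity". IX.2 describes Kaplan-Meier estimation for time-to-event parameters but does not name late toxicity among them. IX.5 promises a sensitivity analysis of attrition and an imputation method still to be proposed; a maximum-bias approach and multiple imputation are among the candidates.

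**The concern.** Recurrence is a foreseeable event that removes patients from the visits at which the primary endpoint is measured, and the protocol itself imposes the removal. A patient who recurs at 6 months has about 18 months of late-toxicity risk left, and no scheduled assessment covers it. The allowance up to 90 patients is explained only by loss to follow-up.

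The stated estimator is a plain proportion, so these patients must be given some value, and the protocol gives none. Counted as non-events, they make the treatment look safer as disease control worsens. Dropped, they make it look more toxic, and the number evaluated may fall below the 67 required by IX.1. Sites also face two instructions that cannot both be followed literally: vital status only, or adverse event reporting to 2 years.

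**Working it through.** **The plan's own figure.** One-stage Fleming, 5% against 15%, one-sided α = 0.05, β = 0.10:

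N = [(1.645·√(0.05·0.95) + 1.282·√(0.15·0.85)) / 0.10]² = 66.6, so 67. This agrees with IX.1.

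**Decision limits.** Under IX.1 the treatment passes with ≤5/67. Under IX.3 with n = 90, the exact 95% upper limit is 13.9% for 6/90 and 15.4% for 7/90, so it passes with ≤6/90. With full observation and no deaths at a true 15%, the chances of passing are 5.1% and 1.3%.

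**Inputs for recurrence.** The local control range of 80–90% in IX.1 implies 10–20% local failure at 2 years, before regional or distant recurrence. The brachytherapy series cited in I.2.1 reports that the "local control rate at 2 years was 79% and at 5 years was 76"%, with 72% overall survival at 2 years. The protocol gives no figure for any first recurrence in this population. I therefore assume R = 15–30% recurrence and D = 5–10% other death at 2 years.

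**Model (assumptions).** True late toxicity is 15%, onset is uniform over 3–24 months, hazards are constant, and toxicity, recurrence and other death are independent. With λR = −ln(1−R)/24 and λD = −ln(1−D)/24:

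- mean share observed at hazard h: m(h) = (e^(−3h) − e^(−24h)) / (21h)
- crude rate, unobserved counted as non-events: 0.15 × m(λR + λD)
- rate with follow-up to death: 0.15 × m(λD)
- rate if patients unobserved to 24 months and without an event are excluded: crude / [crude + 0.85(1−R)(1−D)]

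For R = 15% and D = 5%, λR = 0.00677 and λD = 0.00214. Then m(0.00891) = 0.888, giving 13.3%, and m(0.00214) = 0.972, giving 14.6%. Exclusion gives 0.1332 / (0.1332 + 0.85 × 0.8075) = 16.3%.

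| R / D | Followed to death | Crude | P(≤6/90): followed → crude | P(≤5/67): followed → crude | Excluded: rate (mean n of 90) |
|---|---|---|---|---|---|
| 15% / 5% | 14.6% | 13.3% | 1.7% → 3.6% | 6.2% → 10.3% | 16.3% (74) |
| 20% / 8% | 14.3% | 12.7% | 2.0% → 5.2% | 6.9% → 13.3% | 16.8% (68) |
| 30% / 10% | 14.1% | 11.6% | 2.2% → 8.9% | 7.4% → 19.3% | 17.9% (59) |

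The baseline here is follow-up to death, because toxicity cannot occur after death.

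**Cross-check with a cruder model.** Let a fraction f stop assessment and let a share s of their risk go unseen. The observed rate is 0.15 × (1 − f·s). With s = 0.5, f = 10% gives 14.3% and f = 30% gives 12.8%. P(≤5/67) is then 7.1–12.9% against 5.1%, and P(≤6/90) is 2.1–5.0% against 1.3%. The direction is the same and the size smaller.

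**The case against.** Four points on the other side carry weight.

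First, a reader might infer that patients who recur or die are counted as toxicity-free, so that the primary rate is certainly biased down. The protocol does not say this. Intention to treat fixes the population, not the value given to an unobserved patient, and IX.5 leaves imputation open. The direction depends on a rule that has not been written.

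Second, a reader might infer that late toxicity is not recorded at all after recurrence. XI.2.1 and XI.2.2 do not support that. The definition of a serious event in XI.1.2 covers hospitalization, disability and events the investigator judges medically relevant, so much grade ≥3 late toxicity could still be reported. The cover is incomplete, however. XI.1.2 removes hospitalization or surgery for treatment of the disease from serious event reporting. Non-serious grade 3 events depend on spontaneous entry, without a scheduled visit. And VI.5.3 tells sites the opposite.

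Third, death should not be grouped with recurrence. Counting a death as no event is a legitimate cumulative incidence.

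Fourth, an estimator alone could repair most of this. In a simulation under the same assumptions, an Aalen-Johansen estimate that censors at recurrence gives 14.6%, 14.4% and 14.2%, against 14.6%, 14.3% and 14.1% with full follow-up. An analysis plan could adopt it. That result rests on independence of toxicity and recurrence, which cannot be examined if nothing is collected after recurrence. It also departs from the crude rate that IX.1 and IX.3 describe.

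Stopping grading at recurrence also has a rationale: after salvage treatment it is hard to attribute toxicity to the stereotactic course. That supports a stated censoring rule at local salvage. It does not support silence about the period before it.

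**Conclusion.** The concern holds in a limited form. Systematic grading for the primary endpoint stops at recurrence in living patients, this contradicts the adverse event sections, and the crude intention-to-treat rate comes with no rule for recurrence. The bias is downward if the unobserved are counted as non-events and upward if they are excluded.

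Under the stated assumptions, the crude rate is about 1.3 to 2.5 percentage points below the rate with follow-up to death (14.6 − 13.3; 14.1 − 11.6). The chance of wrongly passing rises from about 2% to 4–9% under the confidence interval rule, and from 6–7% to 10–19% under the 6/67 rule. These sizes depend on the assumed recurrence, uniform onset and constant hazards. Deaths caused by recurrence are not modelled, and including them would narrow the gap somewhat. At low recurrence the effect is modest.

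This should be fixed, but it does not invalidate the trial. It belongs in the protocol because what is collected is decided there.

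**What to change.** 1. **VI.5.3 and the Table 1 footnote.** Reconcile them with XI.2.1 and XI.2.2. State that grade ≥3 late toxicity (date, grade, attribution) is still recorded after recurrence, at the patient's usual visits, to 24 months or death. State that the start date of salvage treatment is recorded and that serious event reporting continues.
2. **IX.3.** Make the primary estimate the 24-month cumulative incidence (Aalen-Johansen) of first grade ≥3 late toxicity, with death as the competing event. Censor at the last toxicity assessment when toxicity follow-up ends, through loss or the start of local salvage. Recurrence by itself is neither a non-event nor a competing event. Compare the 95% confidence interval with 15% as now.
3. **Sensitivity analyses.** Keep the crude proportion and the maximum-bias (worst-case) analysis that IX.5 already mentions.

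The cost is amendment wording and a short toxicity page for patients who recur, with no added visits. Attribution after salvage stays difficult, censoring at salvage still assumes that toxicity is independent of what led to it, and the reported rate may be slightly higher than the crude one.

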## VI.3. Inclusion assessment

Patients eligible for the trial who have signed their consent to participate will be required to have an **initial work-up within 28 days prior to the start of stereotactic radiotherapy.**

This assessment includes:

- Collection of socio-demographic data
- Collection of major medical and/or surgical history
- Collection of concomitant treatments
- History of ENT cancer (date of diagnosis, location, cTNM, histology, HPV status, tumour surgery data, etc.)
- A sample of the tumour taken during diagnosis or surgery will be sent to the sponsor. The analysis of the HPV (immunohistochemistry p16) status of the tumor will be performed in case it was not done by the center initially.
- Clinical examination including usual weight, day weight and height
- Assessment of general condition according to WHO status (*Annex 2*)
- Smoking status (number of packs/year)
- Alcohol consumption
- Type of feed (solid, liquid, mixed, etc.)
- Tumor bed examination (clinical +/- nasofibroscopy)
- Examination of the mouth, throat and neck. Dental work should be done before treatment begins.
- Pregnancy test in women of childbearing potential: urine or blood test within 14 days (maximum) before starting stereotactic radiotherapy
- Chest CT scan: should be performed only if the time between the date of the initial CT scan and the start date of stereotactic radiotherapy is more than 3 months.

- 508 • EORTC QLQ-C30 and H&N35 questionnaire: To be completed by the patient after inclusion  
 509 and before starting stereotactic radiotherapy.

510 Before a patient is included, you will need to ensure that the following documents/imaging are  
 511 available:

- 512 ❖ *Pre-operative imaging: CT scan or cervicofacial MRI*  
 513 ❖ *The endoscopy report*  
 514 ❖ *The operative report*  
 515 ❖ *The anatomical and pathological report*  
 516

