## 517 **IMPORTANT REMINDER**

518 *The time between the date of surgery of the primary tumor and the date of the first fraction of*  
 519 *stereotactic radiotherapy should be less than or equal to 6 weeks (maximum 8 weeks).*  
 520

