## 521 **VI.4. Assessment during stereotactic radiotherapy** 522 **treatment**

523  
 524 The assessments will be carried out **on the day of the 4th fraction (expected day D8) and the day**  
 525 **of the last fraction (expected day D12).**

526 They include:

- 527 • Clinical examination and weight  
 528 • Assessment of general condition according to WHO status  
 529 • Type of feed (solid, liquid, mixed, etc.)  
 530 • Acute toxicity assessments according to NCI-CTCAE v.4.03  
 531 • Collection of concomitant treatments

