| Examen ORL
(bouche, gorge et cou)                                                                                                                                                                                                                                                                                                                                                                                                 | X                                    |                                |       | X                                                 | X          | X                | X                              | X               | X                 | X                 | X                 | X                 | X                 |
| Examen du lit tumoral
(clinique +/- nasofibroscopie)                                                                                                                                                                                                                                                                                                                                                                              | X                                    |                                |       | X                                                 | X          | X                | X                              | X               | X                 | X                 | X                 | X                 | X                 |
| Toxicités (CTCAE v.4,03)                                                                                                                                                                                                                                                                                                                                                                                                             |                                      | Recueil des toxicités aiguës   |       |                                                   |            |                  | Recueil des toxicités tardives |                 |                   |                   |                   |                   |                   |

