#### 1123 ***XI.2.2 Methods for the collection and evaluation of adverse events***

1124 All serious and non-serious ARs should be reported in the case report form on the "Adverse events"  
 1125 page, indicating that they are an SAE (if applicable).

1126 The following criteria must be recorded for each event in the eCRF:

- 1127 ❖ A description of the AR in standard medical terminology, not as reported by the patient
- 1128 ❖ The start date
- 1129 ❖ The recovery date
- 1130 ❖ The grade assessed by the investigator according to the definitions of the NCI-CTCAE,  
 1131 Version 4.03 (*Appendix 1*)
- 1132 ❖ The causal relationship between the event and the research, as assessed by the investigator:

- Linked to a pre-existing or underlying pathology
- Research-related (stereotactic radiotherapy)
- Related to other treatments (specify products)
- Other (e.g. accident, new pathology)
- ❖ Measure taken concerning stereotactic radiotherapy (none, discontinuation, dose reduction, temporary interruption, etc.).
- ❖ Another action.
- ❖ Evolution according to the following definitions:
  - Recovery with sequelae
  - Recovery without sequelae
  - Improvement
  - Persistence
  - Aggravation
  - Death
  - Unknown
- ❖ Serious: yes or no

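### No CTCAE grade is scheduled before radiotherapy in recently operated patients, so the primary endpoint relies on attribution without a graded baseline

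*Protocol*

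**What the plan says.** **Endpoint.** Protocol IV.1 counts patients with grade ≥3 toxicity under the CTCAE v4.03 "classification in connection with hypofractionated stereotactic radiotherapy", arising more than 3 months after the end of treatment.

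**Timing of grading.** In Table 1 the toxicity row is empty at V0. Acute collection ("Recueil des toxicités aiguës") covers the on-treatment and early follow-up visits, and late collection begins at the 6-month visit. Section VI.4 puts the first grading "on the day of the 4th fraction (expected day D8"), when three fractions have already been given.

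**What is collected at V0.** Section VI.3 requires an "initial work-up within 28 days prior to the start of stereotactic radiotherapy". It includes "Clinical examination including usual weight, day weight and height", "Type of feed (solid, liquid, mixed, etc"), tumour-bed and ENT examination, medical history, and the QLQ-C30 and H&N35. No CTCAE grade is listed.

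**Surgery.** The reminder after VI.3 says that the interval from surgery to "stereotactic radiotherapy should be less than or equal to 6 weeks (maximum 8 weeks"). V.1 requires surgical exploration of the neck, and VIII.1.6.1 provides for flap reconstruction.

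**Attribution.** VI.7 has the investigator grade each toxicity and judge whether radiotherapy may have caused it. It singles out seven: mucositis, dysphagia, dry mouth, mandibular osteonecrosis, soft tissue necrosis, epidermatitis and fibrosis. The causality field in XI.2.2 offers pre-existing or underlying pathology, the research (stereotactic radiotherapy), "Related to other treatments (specify products"), and other. Under XI.2.4 the sponsor also decides imputability.

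**The concern.** Several of the seven toxicities, among them dysphagia, fibrosis and soft tissue damage, can also follow the operation that every patient has just had. Without a CTCAE grade before the first fraction, there is no reference on the endpoint's own scale for calling a late grade ≥3 finding new or worse. The protocol also gives no rule for a condition already present at V0.

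The error can go in two directions. A persisting surgical sequela can be counted as radiotherapy toxicity. A true radiotherapy injury in an operated bed can be put down to surgery and left out. The causality list does not help much: surgery is not named, and the option for other treatments asks for products, which points to drugs. The trial has one arm, so no comparator with the same surgery absorbs the error. The verdict turns on a handful of events.

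An analysis plan cannot repair this later, because it cannot supply a baseline grade that the visit schedule never collects.

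**Working it through.** **Inputs from the protocol (IX.1, IX.3).** Acceptable rate 5%, unacceptable rate 15%, one-sided α 0.05, power 90%, N = 67, treatment unacceptable at 6 or more of 67 events, 90 patients enrolled. IX.3 calls the trial positive if the 95% CI excludes 15%; a favourable result therefore needs the upper limit below 15%.

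**1. The plan's own figure.** One-sample normal approximation with 5% as the null:

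n = [(1.645·√(0.05·0.95) + 1.282·√(0.15·0.85)) / 0.10]² = [(0.3585 + 0.4576)/0.10]² = 66.6, so 67. The stated N reproduces. A baseline grading does not change it.

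**2. How many events decide the trial.**

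- IX.3 with 90 evaluable patients, exact (Clopper-Pearson) upper limits: 6/90 gives 13.9%, 7/90 gives 15.4%. A favourable result needs at most 6 events.
- IX.1: at most 5 of 67.

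**3. Surgical sequelae counted as radiotherapy toxicity.** Assumption: the true radiotherapy-related rate is 5%, and a further share s of patients is wrongly counted, without overlap, so the observed rate is 5% + s. P(favourable) is the binomial probability P(X ≤ 6 | 90) or P(X ≤ 5 | 67).

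| s (assumed) | Observed rate | IX.3 rule, n = 90 | IX.1 limit, n = 67 |
|---|---|---|---|
| 0 | 5% | 84% | 88% |
| 1% | 6% | 70% | 79% |
| 3% | 8% | 41% | 55% |
| 5% | 10% | 19% | 33% |

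Here s is the share that gets past attribution. If s is instead the share of patients who have such sequelae, and attribution removes half of them, the observed rates are 5.5%, 6.5% and 7.5%. The IX.3 probabilities are then 77%, 63% and 48%.

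**4. True radiotherapy events put down to surgery.** Assumption: the true rate is 15% and a fraction f of events is dismissed, so the observed rate is 15% × (1 − f).

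| f (assumed) | Observed rate | IX.1 limit, n = 67 |
|---|---|---|
| 0 | 15% | 5.1% |
| 10% | 13.5% | 9.6% |
| 20% | 12% | 17.0% |
| 30% | 10.5% | 28.2% |

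No value of s or f can be taken from the documents.

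**The case against.** The strongest reply is that the protocol already separates the two causes in several ways.

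- IV.1 counts only toxicity arising more than 3 months after radiotherapy and linked to it. XI.2.2 records a start date and a causality category for each event. On a natural reading, dysphagia that began before the first fraction does not qualify.
- Five gradings precede the late window: 4th fraction, last fraction, day 14, day 30 and 3 months. A continuing grade ≥3 sequela should be seen there.
- V0 is not empty. The H&N35 covers swallowing, mouth opening, dry mouth and tube use. History, operative report, feeding type, dental work-up and local examination are also available.
- The investigator is not the only judge, since the sponsor also decides imputability.
- Open-label attribution is inherent in a single-arm phase II trial.

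Most of this stands. A reader might infer from the blank V0 cell that the endpoint cannot separate surgical from radiotherapy morbidity; these provisions show that this goes too far. A reader might also suppose that grade ≥3 surgical morbidity is common at V0, but the documents give no rate. Nor can one conclude that attribution makes the treatment look safer than the brachytherapy and IMRT rates in section I.2. The protocol's summaries do not say how those rates were attributed, and terms such as osteoradionecrosis already imply a radiation cause.

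What the reply does not remove is the gap itself. The V0 information is not on the CTCAE scale, and no rule links it to attribution. The five early gradings all come after treatment has begun, when acute radiotherapy effects may already be mixed in.

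**Conclusion.** The point holds in a limited form. No CTCAE grading is scheduled before radiotherapy, all patients are recently operated, and the causality list does not name surgery. The primary endpoint therefore depends on open-label attribution by investigator and sponsor, with only ungraded baseline information, and the error can go either way.

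Its size is unknown. The percentages above are illustrations under assumed misclassification. They also assume complete evaluability, although the 90 include an allowance for loss to follow-up. They show only that the margin is narrow: with 90 patients, the seventh event turns a favourable result into an unfavourable one, and 1% of 90 is about one patient. They do not show that the trial will reach the wrong conclusion. The gap should be closed because doing so is cheap and the baseline grade cannot be collected prospectively later.

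**What to change.** 1. Add CTCAE v4.03 grading of the seven toxicities named in VI.7 to V0, in both VI.3 and Table 1.
2. In IV.1, count as a primary event a toxicity that reaches grade ≥3 more than 3 months after radiotherapy and is worse than its V0 grade. Say how a toxicity that resolves and then returns to its V0 grade is handled.
3. Name surgery as an option in the causality field of XI.2.2.
4. Report a sensitivity analysis of all new or worsened grade ≥3 late events, whatever the recorded attribution. This is needed as well, because a V0 grade alone does not protect against new radiotherapy injury being put down to surgery.

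**Cost.** One eCRF page at a visit where mouth, throat, neck and feeding are already examined, with no extra visit and no change in sample size. For patients already included, V0 grades must be reconstructed from records and flagged as retrospective. The all-attribution rate may be less favourable than the attributed one.
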